##### The following personnel will remain blinded throughout the trial

4.7.3.1

CBT-I psychologists: Will deliver all CBT-I sessions using a standardized manual without being informed of whether the participant is in the intervention or control group.Independent Outcome assessor (Co-investigator): Will conduct ISI, PSQI, sleep diary review, and follow-up assessments while blinded to the allocation to minimize assessment bias.Statistician: Will perform data analysis using coded datasets. Unblinding will occur only after completion of the final statistical analysis.

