#### Cognitive Behavioral Therapy for Insomnia (intervention and control group)

3.6.3

Participants randomized to the control arm will receive Cognitive Behavioral Therapy for Insomnia (CBT-I) alone for 4 weeks. CBT-I will be delivered twice weekly in 45–60-min individual sessions, either in person or via telehealth, by trained and certified counseling psychologists with a minimum of 2 years of clinical experience. All CBT-I therapists will undergo a protocol orientation meeting prior to study initiation to ensure adherence to the standardized CBT-I manual used in this trial. Session content will be documented after each visit using structured therapist notes. Treatment will follow the same standardized CBT-I manual as described, including sleep restriction therapy, stimulus control therapy, cognitive restructuring, sleep hygiene education, and relapse prevention components.

Participants in the control arm will undergo the same follow-up schedule, outcome assessments, adherence monitoring procedures, and safety oversight as those in the intervention arm to ensure methodological parity between groups. A sham oleation procedure was not included, as standardizing a credible placebo tactile intervention was considered impractical in the context of this exploratory trial.

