##### Intervention phase (weeks 0–4)

4.4.1.1

Active AE screening will occur at every in-person or telehealth contact.A structured ADR/AE checklist will be completed weekly.Participants will be specifically asked about new or worsening symptoms.DSTED diary entries include prompts for reporting discomfort or unexpected symptoms.

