#### Sequence generation

4.7.1

The random allocation sequence will be generated prior to participant enrollment by an independent statistician using R statistical software (version 4.1.5). Block randomization with a fixed block size of 4 will be used to ensure balanced allocation between study arms throughout recruitment. The allocation ratio will be 1:1 (Intervention Group: Control Group). No stratification factors will be applied. The statistician will not be involved in recruitment, intervention delivery, or outcome assessment.

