##### Personnel who cannot be blinded (due to study procedures)

4.7.3.2

Participants: Cannot be blinded because only the intervention group receives visible Ayurvedic therapies (*Siro-pichu* and *Padabhyanga*), while the control group does not.Co-investigators as Ayurvedic intervention providers: Cannot be blinded because they directly administer and train participants in *Siro-pichu* and *Padabhyanga* procedures.Medical Officer/Designated Research Staff: Responsible for maintaining the allocation list, distributing intervention kits (*Kṣirabala Taila*), and ensuring allocation concealment. This person will not be involved in outcome assessment or data analysis. This structured approach ensures rigorous randomization, allocation concealment, thereby maintaining methodological integrity and minimizing potential biases throughout the trial.

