#### Quality control and verification

4.8.2

Completed CRFs will be reviewed on the same day by supervising research staff. Within 24 h, the Principal Investigator or designated Co-Investigator will verify completeness, internal consistency, and protocol adherence.

ADR/AE checklists and DSTED entries will be reviewed at each contact. Data verification will occur before entry into the electronic database.

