#### Data management

4.8.5

Data will be collected using standardized paper-based case record forms and validated outcome assessment instruments completed by participants during scheduled visits. The collected data will subsequently be entered into a password-protected Microsoft Excel spreadsheet maintained on a secure institutional computer. The Excel file will be stored within an encrypted folder with restricted user access, limited to the Principal Investigator and the designated Co-Investigator. A separate master linkage file containing participant identifiers will be maintained independently from the analytical dataset in a secured location accessible only to these investigators. The Principal Investigator will oversee all data management procedures and periodically verify the completeness and accuracy of entries. The Co-Investigator will be responsible for entering outcome scores, follow-up notes, and documented observations into the Excel sheet while maintaining blinding where applicable. All participant data will be coded using unique study identification numbers. Only validated instrument scores and documented clinical observations will be included in the final analytical dataset. The Statistician, who remains blinded to group allocation, will receive an anonymized dataset exported from the Excel file for analysis according to the pre-specified statistical analysis plan. Regular backups will be maintained on secure institutional servers to ensure data integrity and prevent data loss. Role-based access restrictions will be implemented throughout the study to maintain confidentiality.

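### Coding alone cannot keep the statistician blinded to the end of the planned analysis, and the CBT-I therapists' blinding is left unprotected

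*Protocol article*

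**What the plan says.** Section 4.7.3.1 lists three roles as blinded for the whole trial: the CBT-I psychologists, the outcome assessor and the statistician. The psychologists deliver their sessions "without being informed of whether the participant is in the intervention or control group". For the statistician the section adds: "Unblinding will occur only after completion of the final statistical analysis". Section 4.8.5 gives the mechanism: "The Statistician, who remains blinded to group allocation, will receive an anonymized dataset exported from the Excel file for analysis". The columns of that export are not listed.

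Other sections bear on these claims:

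- **Adherence.** Section 3.9.1 sets an 80% threshold for the oil applications, recorded in the Daily Sleep and Treatment Engagement Diary (DSTED). Section 4.9.2 has adherence percentages compared between groups, and section 4.10 adds a per-protocol analysis to the ITT analysis.
- **Opening the codes.** Section 4.7.2 ties this to the end of the post-intervention assessments, or earlier in a medical emergency.
- **Contacts.** Section 3.6.3: "CBT-I will be delivered twice weekly in 45–60-min individual sessions, either in person or via telehealth". Section 4.4.1.1: "Active AE screening will occur at every in-person or telehealth contact". Section 4.8.2: "ADR/AE checklists and DSTED entries will be reviewed at each contact".
- **Participants.** Section 4.7.3.2: "Cannot be blinded because only the intervention group receives visible Ayurvedic therapies".

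**The concern.** A group code blinds an analyst only while no other variable in the dataset belongs to one arm by construction. Here one does: completion of the oil procedures.

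The statistician still has decisions to make after seeing data. Section 4.9.1 lets the distribution decide between a t-test and a Mann–Whitney test, section 4.10 triggers multiple imputation above 10% missing, and the per-protocol set has to be formed. Blinding is meant to ensure that these are settled without knowing which arm a choice favours.

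The therapists matter for a different reason. There is no sham procedure, so the comparison depends on both arms getting the same CBT-I. Therapists set and adjust the sleep prescription, and missed sessions may be made up. If they learn the arm, that background treatment can drift apart. Section 4.7.3 credits the whole process with limiting performance and detection bias, and readers of the results would take it at its word.

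**Working it through.** The point rests on no figure in the plan. As a routine check, the sample size reproduces: 2 × 4.3² × (1.960 + 1.282)² / 4² = 24.3, so 25 per group by the normal approximation and 26 by the t distribution (power 0.908 at 26). Then 26 / 0.85 = 30.6, so 31 per arm and 62 in all. No number is in dispute.

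**Statistician**

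1. Prescribed oil applications in the add-on arm (section 3.6.2): 7 Siro-pichu + 2 × 14 Padabhyanga = 35. In the control arm: 0.
2. An oil-adherence percentage therefore has a denominator in one arm only. In the other it is undefined or blank.
3. The dataset has two group codes. One record with an oil-adherence value shows which code is the add-on arm, and hence the arm of all 62 women.
4. Adherence is a planned between-group analysis with the DSTED as its instrument (sections 4.2 and 4.9.2). Any per-protocol set that uses the 80% oil threshold needs the same data. Both come before the final analysis is complete, which is the moment section 4.7.3.1 gives for unblinding.
5. Nothing in the article puts the primary ISI result before the release of these data.

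**Time of unblinding**

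Section 4.7.2 lets codes be revealed once post-intervention assessments end. Section 4.12 starts all analyses after data collection. On those two sections the codes could be open before any analysis begins; section 4.7.3.1 keeps them closed until the last analysis is done. Section 4.7.2 does not say to whom the codes are revealed, so the two may be compatible, but as written they give different times.

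**Therapists**

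1. Each woman has eight individual sessions, in person or by telehealth. At two a week, about 2 × 2 = 4 fall in Days 1–14, while oil is in daily use (assuming that sessions start at baseline).
2. AE screening is set for every in-person or telehealth contact in Weeks 0–4, and DSTED review for each contact. Neither section names who does it, and neither exempts CBT-I sessions.
3. The DSTED holds the oil log, and the women know their arm.
4. The chance of disclosure is not given. If it is p per session, independent across sessions (an assumption), the chance of disclosure within eight sessions is 1 − (1 − p)^8:

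| p (assumed) | within 8 sessions |
|---|---|
| 1% | 8% |
| 5% | 34% |
| 10% | 57% |
| 20% | 83% |

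This shows how a small chance accumulates. It does not estimate what will happen.

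**The case against.** **The therapist part is inference.** A reader might conclude that the plan's data flow discloses the arm to the therapists. The documents do not support that. No section gives AE screening or DSTED review to therapists. Section 4.8.1 has the instruments completed under staff independent of intervention delivery, section 4.7.3.1 gives sleep-diary review to the blinded assessor, section 4.4.2 has the Principal Investigator evaluate each event, and section 8.6 limits therapists to what their role needs. This stands, and it reduces the point to a risk. It does not remove the risk, since none of these sections keeps the review out of the sessions.

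**Not every variable decodes the arm.** A reader might add SDS scores and AE relatedness to the list. SDS is planned as a between-group comparison, so having a score does not mark an arm. Relatedness is rated against the study intervention, and section 4.14 also mentions psychotherapy and study procedures. Only oil adherence clearly decodes.

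**The export could omit it.** If per-protocol status rested on CBT-I attendance alone and someone else summarised oil adherence, the code could survive. The article says neither.

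**The sequence generator might be the analyst.** Section 4.7.1 says "The statistician will not be involved in recruitment, intervention delivery, or outcome assessment", which does not mention analysis. That does not show that one person does both.

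**Inflated error.** A reader might attribute a raised false-positive rate to the unblinding. Choosing the smallest of several two-sided p-values does not depend on which arm is which, so a blinded analyst could inflate the error just as much. ITT is also fixed as primary.

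**Low consequence.** ISI and PSQI are self-administered by women who know their arm, p-values are descriptive, and all outcomes are exploratory. This stands.

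**Conclusion.** The statistician's blinding cannot last to the end of the final analysis by coding alone. It fails for all 62 women once oil-completion data are released, assuming that the same statistician does the adherence or oil-based per-protocol analysis on the coded export. The primary Week 4 ISI comparison can still be done blind if the order of release is fixed. The two stated times of unblinding need reconciling.

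For the CBT-I therapists, the conclusion is that blinding is claimed but not protected: the reviewer at each contact is unnamed and the participants are unblinded. Actual disclosure is not shown.

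No bias in ISI points can be derived from the documents. The consequence is modest, because self-report by unblinded women is the larger route to bias. The repair is still worth making, since it costs little and the safeguards would otherwise be reported as stronger than they are.

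**What to change.** 1. **Release data in two steps.** First export baseline, ISI and PSQI data with a dummy arm code. Fix the choice of test and lock the primary Week 4 ISI result. Only then release oil-adherence, AE and SDS data.
2. **Reconcile sections 4.7.2 and 4.7.3.1** on when codes are revealed, and say to whom.
3. If step 1 is not adopted, restate that the statistician is blinded for the primary analysis only. That statement also needs the oil data held back until the primary analysis is done.
4. **Name the reviewer.** State in sections 4.4.1.1 and 4.8.2 that AE and DSTED review is done by non-therapist research staff, outside the CBT-I sessions. It should not be handed solely to the unblinded intervention providers, which would conflict with sections 4.7.3.1 and 4.8.1.
5. **Split the diary.** Keep the oil-completion page apart from the sleep page that therapists or the blinded assessor see, and ask women not to mention their allocation to either.
6. If steps 4 and 5 are not adopted, soften the therapist claim to not informed by the study team.

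The cost is a re-laid diary form, a line in the participant and staff instructions, and two exports instead of one. If every session is still to carry an AE screen, research staff also need a short check before or after it.

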##### Personnel who cannot be blinded (due to study procedures)

4.7.3.2

Participants: Cannot be blinded because only the intervention group receives visible Ayurvedic therapies (*Siro-pichu* and *Padabhyanga*), while the control group does not.Co-investigators as Ayurvedic intervention providers: Cannot be blinded because they directly administer and train participants in *Siro-pichu* and *Padabhyanga* procedures.Medical Officer/Designated Research Staff: Responsible for maintaining the allocation list, distributing intervention kits (*Kṣirabala Taila*), and ensuring allocation concealment. This person will not be involved in outcome assessment or data analysis. This structured approach ensures rigorous randomization, allocation concealment, thereby maintaining methodological integrity and minimizing potential biases throughout the trial.

### Data collection and management

4.8

#### Data collection procedures

4.8.1

Study data will be captured via standardized paper-based case record forms (CRFs) and validated outcome instruments. Trained research staff, independent of intervention delivery, will oversee data collection at the Outpatient Department (OPD) during screening and baseline. Subsequent intervention (Weeks 2, 4) and follow-up (Weeks 6–16) assessments will occur in person or via telehealth. Outcome instruments (ISI, PSQI, SDS, DSTED) are self-administered by participants under supervision of trained research staff independent of intervention delivery. Research staff may clarify instructions but will not influence responses (Table 1).

**Table 1 tab1:** Data collection methods.

Trial instrument	Purpose	Frequency of measurement	Timepoints of assessment
Insomnia Severity Index	To determine the primary outcome: severity of insomnia symptoms over the preceding two weeks	Every 2 weeks	Baseline (Week 0), Week 2, Week 4 (end of intervention), Week 6, Week 8, Week 12, Week 14, Week 16 (end of follow-up)
Pittsburgh Sleep Quality Index	To evaluate the overall sleep quality and its domains, including latency, duration, efficiency over the past month	Monthly	Baseline (Week 0), Post- treatment (Week 4), Follow-up Months 1, 2, and 3
ADR Monitoring Checklist	To identify and document any adverse events or reactions related to the integrative intervention	Ongoing monitoring at each contact point	Weekly during intervention (Weeks 0– 4), and monthly during follow-up (Months 1–3)
Severity of dependency Scale	To detect any signs of behavioral or psychological dependency on *Śiro-pichu* and *Pādābhyanga* therapies	Twice during the study	Post-intervention (Week 4), End of follow-up (week 16)
Daily Sleep and Treatment Engagement Diary	To assess adherence and consistency in following the prescribed intervention protocol	At the end of intervention and follow up	Week 4 of intervention, Week 16 of follow up

Official Malayalam versions of ISI and PSQI were obtained from ePROVIDE–MAPI Research Trust (COA request submitted 08-Aug-2025; approval date: 01 September 2025). Instruments will be administered in accordance with licensing terms. Table 1 shows the data collection methods in detail.

Sleep diaries will record total sleep time (TST). For descriptive summaries, TST will be categorized as optimal (7–9 h), short (<6 h), or long (>9 h). Classification is for characterization only and will not determine treatment response.

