### Exploratory secondary objectives

2.2

To determine mean reduction in the Pittsburgh Sleep Quality Index (PSQI) score (42, 43) after 4 weeks of intervention with CBT-I added with external administration of *Siro-pichu* and *Padabhyanga* with *Ksirabala Taila*, compared to CBT-I alone.To determine the early onset of therapeutic response within the first 2 weeks of intervention using the ISI score, with a focus on changes in the severity of insomnia.To determine changes in insomnia severity during the three-month follow-up period, measured at two-week intervals using the ISI score.To determine the sleep quality measured using the PSQI score during the 3 months of follow up.To record the occurrence and severity of ADEs associated with the integrative protocol using a validated ADR monitoring checklist.To determine the potential psychological or behavioral dependency risk related to the adjunctive Ayurvedic therapies (*Siro-pichu* and *Padabhyanga*) using Severity of dependency Scale during the 3-month relapse prevention follow-up phase.To determine treatment adherence in both intervention and control groups using the Daily Sleep and Treatment Engagement Diary.

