### Harms and adverse events monitoring

4.4

Harms will be defined as any untoward medical occurrence, whether or not causally related to the intervention, including adverse events (AEs), adverse reactions, serious adverse events (SAEs), and unexpected events. Adverse events will be systematically recorded using the WHO–UMC (World Health Organization–Uppsala Monitoring Center) causality assessment framework.

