#### Exploratory secondary outcome analysis

4.9.2

Follow-up ISI and PSQI scores beyond Week 4 will be summarized descriptively. Data will be presented as mean ± SD or median (IQR), and graphical trends over time will illustrate within-group patterns. No formal repeated measures ANOVA or confirmatory longitudinal modeling is planned. These analyses are exploratory and not adjusted for multiple comparisons. Sleep-duration categories (<6 h, 7–9 h, >9 h) will be used for descriptive summaries and exploratory subgroup analysis. No confirmatory inference will be based solely on duration categories. Adverse events will be summarized by frequency and proportion in each group. Between-group comparisons will be explored using Chi-square or Fisher’s exact tests. Severity of Dependence Scale (SDS) scores and adherence percentages will be summarized descriptively and compared between groups using appropriate parametric or non-parametric tests. Findings will be interpreted as exploratory.

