### Safety

4.14

All adverse events (AEs) and serious adverse events (SAEs) will be systematically documented in the Case Report Form (CRF) using a predefined Adverse Drug Reaction (ADR) page. Each entry will capture the event description, diagnosis (if available), onset and resolution dates, severity (mild, moderate, or severe), action taken with the study drug (none, temporarily interrupted, or permanently withdrawn), outcome (resolved, resolved with sequelae, or not resolved), and the assessed relationship to the study drug (definite, probable, possible, unlikely, not related, or not assessable). The Principal Investigator and Co-Investigator will independently evaluate causality, taking into account the temporal relationship with the study drug, the participant’s clinical course, medical history, and concomitant medications. All adverse events will be actively managed by the study investigators with access to on-site medical services at the study institution. Escalation will follow institutional clinical pathways, including specialist referral when indicated. Costs of medical management for trial-related adverse events will be borne by the institution in accordance with ethical guidelines.

Events occurring after a participant exits the study will not be routinely reported unless the investigators consider a reasonable likelihood of relation to the study drug, psychotherapy, or study procedures. This systematic documentation ensures continuous monitoring and prioritization of participant safety throughout the trial.

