### Risk–benefit assessment

8.2

The combined intervention (CBT-I with *Siro-pichu* and *Padabhyanga*) is considered low risk. Possible minor risks include transient discomfort, drowsiness, mild skin irritation from medicated oils, or emotional distress during CBT-I. Safety instructions will be provided to minimize risks such as slipping after oil application. Adverse events will be recorded using the WHO-UMC ADR framework and managed promptly. Serious adverse events will be reported to the IEC within 24 h. Potential benefits include improved sleep onset, duration, and quality, reduction in insomnia severity, and better overall wellbeing.

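### Adverse-event relatedness is recorded against a study drug that control women never receive, so harms of CBT-I are not clearly attributed and relatedness cannot be compared between arms

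*Protocol article*

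**What the plan says.** **Scope of collection.** Section 4.4 is broad: "Harms will be defined as any untoward medical occurrence, whether or not causally related to the intervention". Section 4.4.1.1 asks for screening at every contact, a weekly checklist and direct questions about new or worsening symptoms, without limiting any of this to one arm. Section 3.6.3 gives controls the "same follow-up schedule, outcome assessments, adherence monitoring procedures, and safety oversight as those in the intervention arm".

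Two other places are narrower. The objective in Section 2.2 is "To record the occurrence and severity of ADEs associated with the integrative protocol using a validated ADR monitoring checklist". Table 1 in Section 4.8.1 states the purpose of the checklist as "To identify and document any adverse events or reactions related to the integrative intervention".

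**Attribution.** Section 4.4.2 lists a form field for relatedness to the study intervention. Section 4.14 describes the form differently. It records action taken with the study drug, bases the causality judgement on timing relative to the study drug, and captures "the assessed relationship to the study drug (definite, probable, possible, unlikely, not related, or not assessable". Psychotherapy appears there as a possible cause only in the rule for events after a participant has left the study.

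**Known risks.** Section 8.2 lists "mild skin irritation from medicated oils, or emotional distress during CBT-I" among the possible minor risks.

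**Analysis.** Section 4.2 plans adverse events by frequency and proportion in each group, with severity and relatedness described. Section 4.9.2 adds: "Between-group comparisons will be explored using Chi-square or Fisher’s exact tests".

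**The concern.** Both arms receive the same CBT-I and only one receives the oil procedures. To describe the safety of the add-on, the trial has to separate events that belong to the shared therapy from events that belong to the oil. The Section 4.14 form offers one rating, against an exposure that only the add-on arm has. A CBT-I harm then has no natural place on the form in a control woman, and in an add-on woman it may be credited to the oil.

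Safety is one of the trial's stated purposes, and relatedness is part of the safety output. A relatedness judgement is also hard to reconstruct reliably once paper forms have been completed. Separately, an objective and a checklist purpose that are narrower than the governing definition invite staff to filter events by cause.

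**Working it through.** No formula applies. The only count needed is the share of participants without a study drug: 31 controls out of 62, or 31/62 = 50%. The rest is a comparison of sections.

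1. **Is collection all-cause in both arms?** Sections 4.4, 4.4.1.1 and 3.6.3 together say yes, and Section 4.4.2 and the opening of Section 4.14 both refer to all adverse events. Sections 2.2 and 4.8.1 (Table 1) restrict the objective and the checklist's purpose to the integrative protocol or intervention. The abstract uses the integrative arm as the name of the add-on group. Even if integrative means CBT-I plus oil, it is a package that controls do not receive. These two places contradict Section 4.4.

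2. **What is relatedness judged against?** Section 4.4.2 says the study intervention and Section 4.14 says the study drug. The first term is not settled either: Section 4.12 describes the intervention as CBT-I, while Section 4.7.1 uses Intervention Group for the add-on arm. The discontinuation rule in Section 4.4.3 depends on relatedness to the intervention and so inherits the ambiguity.

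3. **Trace one event.** Suppose one woman in each arm reports emotional distress during a CBT-I session in the first two weeks.
   - Under Sections 4.4, 4.4.1.1 and 3.6.3 both events are recorded, and the count is 1 v 1.
   - Under Section 4.4.2 both can be rated if the intervention means CBT-I. Only the add-on woman's event can be rated meaningfully if it means the oil procedures.
   - Under Section 4.14 the add-on woman's event may take any of the six categories. The control woman had no study drug, so hers can only be not related or not assessable.

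4. **Can timing separate the causes in the add-on arm?** Not in the first two weeks. The oil procedures run on Days 1–7 and 1–14 (Section 3.6.2). CBT-I sessions are twice weekly and sleep restriction is introduced at Session 2 (Sections 3.6.3 and 3.6.3.1), so on schedule it begins in the first week. An event in that window follows both exposures, but Section 4.14 asks about one.

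5. **Which planned output is affected?** The frequency comparison in Section 4.9.2 uses counts of adverse events, and step 3 gives the same count in each arm whatever the rating. The relatedness summary by group in Section 4.2 is affected, because the same event takes values from different sets of categories in the two arms.

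**The case against.** The strongest reply is that the operational sections already provide what is needed. The harms definition is independent of cause, the screening schedule is not limited by arm, and controls have the same safety oversight. Section 4.4.2 has a relatedness field that is not tied to a drug. The between-arm test concerns frequency, with relatedness only described. The Table 1 entry is a short purpose cell in which the restriction might qualify reactions alone, and integrative may include CBT-I. Form design can also be left to the full protocol or the case report form.

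Much of this stands. A reader might infer from Table 1 and Section 4.14 that adverse events are collected only for the oil therapy, that control events go uncounted, and that the arm comparison is therefore one-sided. The article does not support that: it would require staff to disregard Sections 4.4, 4.4.1.1 and 3.6.3 for every control participant. It would also go too far to say that CBT-I harms have no attribution at all, given Section 4.4.2, or to treat the symptoms in Section 3.10.1 as CBT-I harms, since that section assigns them to no cause. Only Section 8.2 names a CBT-I risk as such.

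The reply does not remove the conflict between Sections 4.4.2 and 4.14. This is not a detail left out of a condensed article: Section 4.14 spells out the fields, and they do not fit the control arm.

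**Conclusion.** The point holds as a defect of attribution and wording. The safety objective and the Table 1 purpose contradict the harms definition. The causality and action fields in Section 4.14 have no referent for the 31 control women and disagree with Section 4.4.2. Relatedness to CBT-I is not clearly captured in either arm, and the relatedness summary by group would not be comparable.

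The comparison of all-cause frequencies is sound, provided that Sections 3.6.3, 4.4 and 4.4.1.1 govern what staff record. No numerical size can be given: the article contains no expected adverse-event rate, and any figure for lost control events would rest on an assumption that its own procedures contradict. The conclusion on attribution assumes that the form follows Section 4.14 as written. If the actual form uses the Section 4.4.2 field with a clear definition covering CBT-I, what remains is the need to correct the text.

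**What to change.** - Reword the safety objective in Section 2.2 and the checklist purpose in Table 1 to cover all adverse events in both arms, regardless of cause, as in Section 4.4.
- In Section 4.14, replace the study-drug entries for relatedness and action taken with separate entries for CBT-I and for the oil procedures, the latter marked not applicable in controls. Use the same terms in Section 4.4.2.
- State in Section 4.9.2 that the between-arm comparison uses all-cause adverse events, and in Section 4.2 that relatedness is described per component.
- Reconcile what the intervention refers to in Section 4.4.3 with Sections 4.4.2 and 4.14. No change to the clinical rule itself is proposed here.

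The cost is rewording, one added field on the paper adverse-event form and slightly more data entry. Because an oil entry marked not applicable reveals the arm, that page should be kept from the blinded outcome assessor.
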